## Abstract

**Background:**

Cardiovascular diseases (CVDs) remain the leading cause of morbidity and mortality worldwide. While a substantial proportion of CVD burden is attributable to modifiable risk factors, individual genetic susceptibility also contributes significantly. Polygenic risk scores (PRS) have emerged as promising tools to quantify inherited cardiovascular risk, while digital health technologies, such as wearable health devices (WHDs), provide new opportunities for continuous lifestyle monitoring However, the feasibility of integrating PRS and WHDs into primary prevention within public healthcare systems has not yet been systematically evaluated.

**Objective:**

The FitPreV study aims to assess the feasibility of implementing PRS and WHDs in cardiovascular primary prevention among individuals with metabolic syndrome in the Italian National Health Service (SSN), focusing on their acceptability, practicality, and barriers to adoption in general practice.

**Methods:**

FitPreV is a pilot, four-arm, randomized controlled feasibility study involving 120 adults aged 40–69 years diagnosed with metabolic syndrome and an estimated 10-year CVD risk between 2.5 and 10%. Participants will be randomly assigned to: (1) standard counseling; (2) counseling plus WHD; (3) counseling plus PRS; or (4) counseling plus both PRS and WHD. Data will be collected at baseline, 1, 6, and 12 months. Feasibility indicators include recruitment and retention rates, acceptability, burden and structural readiness. Secondary outcomes include changes in lifestyle behaviors, lipid profiles and cardiovascular risk (SCORE2 algorithm).

**Expected results:**

The study will generate evidence on the operational feasibility and acceptability of integrating genetic risk assessment and digital monitoring tools into primary cardiovascular prevention within general practice settings.

**Conclusions:**

By evaluating real-world implementation challenges, FitPreV will provide foundational evidence to guide larger-scale effectiveness trials studying personalized prevention approaches into national primary care settings.

**Trial registration:**

https://clinicaltrials.gov/study/NCT06911294, identifier: NCT06911294.

## Introduction

Cardiovascular diseases (CVDs) encompass a wide array of conditions, including coronary artery disease, heart failure, and stroke, which arise from the complex interplay of numerous genetic variants, unhealthy lifestyles and diet (1) and socioeconomic factors (2). CVDs pose a significant global health concern (3), as they are the leading cause of death and illness both in Europe and worldwide (4). Significant progress in CVDs management, coupled with heightened awareness of the value of preventive strategies, has contributed to a global decline in age-standardized incidence and mortality rates. Nevertheless, as the population ages and grows, the absolute number of CVDs incident cases and deaths has increased over time (5). A considerable portion of the burden of CVDs can still be attributed to modifiable risk factors, including elevated systolic blood pressure, high levels of LDL cholesterol, and tobacco use (6). This highlights the importance of sustained efforts in counteracting CVDs and in the development of innovative strategies for prevention (7). In this context, personalization represents a cutting-edge area of medical research, enhancing population health while potentially lowering expenses for healthcare systems. Polygenic risk scores (PRS) have recently attracted attention for their ability to quantify an individual's genetic predisposition to CVDs (8). By identifying subjects with high inherited risk, PRS could enable earlier and more targeted preventive interventions, complementing traditional risk stratification tools (8). This is particularly relevant for individuals with metabolic syndrome, a cluster of conditions including central obesity, dyslipidemia, elevated blood pressure and hyperglycemia, that markedly increases CVD risk (9). Such individuals represent a population in which combining genetic information with lifestyle monitoring could be particularly impactful, as an unfavorable polygenic architecture may synergize with metabolic and behavioral risk factors, thereby amplifying the lifetime cardiovascular risk trajectory and potentially accelerating the onset of major adverse cardiovascular events. Similarly, this population can take advantage of digital health technologies, such as wearable health devices (WHDs) capable of monitoring physical activity, dietary, and sleep habits giving the patient a feedback that could nudge him further toward healthy habits (10). Nevertheless, in order to facilitate the implementation of new health technologies and interventions, in addition to their efficacy currently under investigation in an ongoing trial (11), it is necessary to demonstrate their feasibility, considering factors that can prevent their adoption. These factors encompass among others, acceptability, demand, implementation, practicality (12), and their assessment can be useful for both refining methods to evaluate their efficacy and developing implementation strategies (13). To date, no study has evaluated whether PRS, alone or combined with WHDs, can be feasibly adopted within primary prevention programs for CVDs. The present paper describes the rationale and design of the FitPreV trial, a feasibility pilot randomized controlled study assessing the integration of PRS and WHDs in primary prevention for individuals with metabolic syndrome within the Italian National Health Service (SSN).

### General objective

The FitPreV study aims to evaluate the feasibility of implementing PRS and WHDs for CVD primary prevention within the SSN. Aligning with the PNRR's focus on proximity healthcare (Mission 6, Component 1) (14) the trial will assess their integration in General Practitioners' (GPs) practices. The study will target individuals with metabolic syndrome, a population at substantially increased CVD risk and potentially receptive to lifestyle interventions, with the goal of assessing the acceptability, practicality, and barriers to adoption of these innovative tools in a real-world primary care setting.

### Primary objective

Evaluate the feasibility of implementing PRS and WHDs in personalized cardiovascular prevention prompted by GPs.

### Secondary objectives

The secondary objectives include a preliminary assessment of the clinical impact of PRS and WHDs on cardiovascular prevention (15).

## Methods

This protocol is written according to the SPIRIT statement (16, 17).

The feasibility study employs a randomized controlled design with four parallel arms in a cohort of patients residing in the metropolitan area of Rome. Participants will be randomly allocated to one of the following intervention groups:

° The first group will receive standard medical counseling (Control group).° The second group will receive standard counseling along with a wearable device and corresponding app (Wearable device group).° The third group will receive standard counseling plus genetic risk information (PRS) obtained from saliva samples (Genetic risk group).° The fourth group will receive standard counseling, genetic risk information and a wearable device (Combined group).

A detailed explanation of each of the interventions can be found in the “Interventions” section.

### Trial population and setting

The population will be composed of 120 participants aged 40 to 69 years with a diagnosis of metabolic syndrome and a 10-year CVD risk between 2.5 and 10%, who are under the care of GPs in Rome metropolitan area 2025–2026 (Italy).

### Inclusion criteria

Participants must meet the following criteria:

Aged 40–69 years.SCORE2 10-year cardiovascular risk of 2.5%−10%.Diagnosis of metabolic syndrome according to American Heart Association (AHA) criteria, chosen for feasibility in primary care as it uses routinely collected data^9^.Specifically AHA criteria require the presence of at least three of the following:
° Central obesity (waist circumference greater than 102 cm in men or greater than 89 cm in women).° Elevated triglycerides (≥150 mg/dL) or treatment for hypertriglyceridemia.° Low HDL cholesterol (less than 40 mg/dL in men or less than 50 mg/dL in women) or treatment for dyslipidemia.° Elevated blood pressure (systolic ≥130 mmHg or diastolic ≥85 mmHg).° Elevated fasting blood glucose (≥100 mg/dL) or treatment for hyperglycemia.

### Exclusion criteria

Individuals with any of the following conditions will be excluded from the study:

Diabetes mellitus.Familial hypercholesterolemia.Previous cardiovascular events.

### Primary endpoints

The feasibility indicators as detailed in their section.

### Secondary endpoints

Lifestyle changes measured through the LF8 questionnaire (18), changes in cardiovascular risk profiles evaluated through SCORE2 (15), biochemical variations including glucose, total cholesterol, HDL cholesterol, LDL cholesterol, triglycerides and glycated hemoglobin (HbA1c).

### Study procedures

The study procedures will follow a structured timeline involving multiple assessments and interventions (see Figure 1).

**Figure 1 F1:**
[figure not shown]
Study flow and timeline of the Fitprev pilot feasibility trail. WHD, wearable health device; PRS, polygenic risk score.

#### Pre-screening

GPs will generate a preliminary list of eligible patients by querying their electronic health records (i.e., the practice's digital management systems for clinical data). Potentially eligible individuals will be contacted and invited to their GP's practice, where the study will be explained in detail. At the in-person visit, an additional verification of the inclusion and exclusion criteria will be performed.

#### Enrolment (T0)

GPs will provide verbal and written informed consent to eligible individuals, including specific modules for genetic analysis. Then, participants will be formally enrolled and randomly assigned to one of the four study arms using a computer-generated randomization procedure implemented through the REDCap (Research Electronic Data Capture) system, which will also record all participants information during the study. The assignment to the intervention will not be blinded. Participants, research staff, and the medical team will become aware of study group allocation only after completion of the randomization procedures. Given the nature of the intervention, blinding of participants and healthcare professionals is not feasible, as participants will know whether they receive PRS information and/or access to the app and wearable device. Outcome assessment cannot be fully blinded, particularly for self-reported behavioral outcomes, because these outcomes are directly provided by participants who are aware of their allocation. Standardized study materials and instructions will be provided to GPs to support consistency in intervention delivery across study arms.

All participants will undergo a comprehensive assessment and cardiovascular evaluation. This will include the completion of questionnaires covering socioeconomic status, area of residence and key lifestyle factors such as smoking, alcohol consumption, dietary patterns, sleep and physical activity. Cardiovascular health will be assessed using the Life's Essential 8 (LE8) framework (18) developed by the American Heart Association (AHA), which encompasses eight domains: physical activity, nicotine exposure, sleep health, body mass index, blood lipids, blood glucose, blood pressure and diet (Annex 1, section 1, section 2, section 3). Each component is scored on a continuous scale from 0 to 100 according to AHA criteria. The overall LE8 score is calculated as the unweighted mean of the eight components, resulting in a composite score ranging from 0 to 100, with higher values indicating more favorable cardiovascular health. In line with AHA classification, scores will be categorized as poor (0–49), intermediate (50–79), or ideal (80–100). Dietary quality will be assessed using the modified Mediterranean Eating Pattern for Americans (MEPA) (19). Based on the LE8 assessment, participants will be categorized into favorable, intermediate, or unfavorable lifestyle profiles.

Additionally, participants will be asked questions to assess their perceptions of cardiovascular risk and the perceived benefits of preventive interventions (20). All questionnaires are provided in Appendix 1.

For participants assigned to groups 3 and 4, saliva samples will be also collected to conduct PRS analysis to evaluate their genetic risk profile for CVD.

For participants in groups 2 and 4, wearable devices will be provided along with instructions on how to set up and use the accompanying mobile application.

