Exploratory analysis will be conducted to provide preliminary insights into potential effects of the interventions on lifestyle behaviors, lipid profiles, and cardiovascular risk. For this purpose, the three intervention groups will be compared with the control group to estimate the marginal effect of each intervention and their combination. Mixed-effects models for repeated measures will be employed to assess within- and between-group differences over time for continuous outcomes, such as lifestyle scores, lipid levels, and SCORE2 cardiovascular risk estimates. These models will include fixed effects for group, time, and their interaction, and random effects for participants to account for intra-individual correlation. Given that participants are nested within GPs, potential GP-level clustering will be explored by including GP as a random effect, where appropriate. Models will adjust for baseline values and stratification factors. Effect estimates will be presented as mean differences with 95% confidence intervals, recognizing that the study is not powered for hypothesis testing. Effect estimates will be presented as mean differences with corresponding 95% confidence intervals. Given the exploratory nature of the analyses, emphasis will be placed on the magnitude and precision of the estimates rather than on formal hypothesis testing. All analyses will be performed using Stata (StataCorp. 2025. Stata Statistical Software: Release 19. College Station, TX: StataCorp LLC) and R (https://www.r-project.org/). In respect to the qualitative interviews, recordings will be analyzed using thematic analysis through a double-coding approach.

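### As the T0 text is ordered, open randomisation comes before the self-reported baseline questionnaires, so the lifestyle baseline used for adjustment may be answered with the arm known

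*Protocol article*

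**What the plan says.** The protocol article, section Enrolment (T0), starts with consent and goes straight on: "Then, participants will be formally enrolled and randomly assigned to one of the four study arms". It adds that "The assignment to the intervention will not be blinded", and on timing: "Participants, research staff, and the medical team will become aware of study group allocation only after completion of the randomization procedures".

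A new paragraph then says: "All participants will undergo a comprehensive assessment and cardiovascular evaluation". This covers "key lifestyle factors such as smoking, alcohol consumption, dietary patterns, sleep and physical activity" and the LE8 score, the unweighted mean of eight components. After that, "participants will be asked questions to assess their perceptions of cardiovascular risk and the perceived benefits of preventive interventions". Saliva collection (groups 3 and 4) and device hand-out (groups 2 and 4) come last.

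The Pre-screening section places only the records query, the explanation of the study and the check of eligibility criteria ahead of enrolment.

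In Statistical analysis, the exploratory mixed models cover lifestyle scores, lipid levels and SCORE2, and "Models will adjust for baseline values and stratification factors".

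**The concern.** Adjusting for a baseline value is safe when the value was fixed before anyone knew the arm. If the T0 steps are carried out in the order in which they are described, participants report their diet, activity, sleep and smoking after learning whether they will get a device, a genetic result, both or neither. That knowledge can change the answers. A covariate affected by allocation then carries part of the allocation effect into the adjustment and biases the comparison between arms.

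The article does concede, in Enrolment (T0) and in the limitations part of the Discussion, that self-reported outcomes are open to bias because blinding is not possible. Neither place mentions the baseline. Reporting at follow-up is unavoidably unblinded in this trial, whereas reporting at baseline need not be. The lifestyle estimates are meant to inform a definitive trial and are to be read for their magnitude and precision, so an avoidable systematic error in them is worth removing.

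**Working it through.** **Order of steps.** Taken in text order, T0 runs: consent; randomisation and open allocation; lifestyle questionnaires and LE8; risk-perception questions; saliva and devices by arm. No visible sentence puts any questionnaire before randomisation or before disclosure of the arm. No sentence explicitly puts them after it either.

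**Which values are exposed.** Of the eight LE8 components, four (physical activity, nicotine, sleep, diet) are taken here as self-reported. The other four (body mass index, lipids, glucose, blood pressure) are measured and little exposed, as are the laboratory endpoints. SCORE2 is an eligibility criterion checked at pre-screening, so its eligibility inputs should predate allocation. Risk perception is not named among the modelled outcomes. For it the issue is a possibly affected T0 measurement and not an affected covariate.

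**Size.** The plan has no figure of its own to reproduce. From the documents: 120 participants, allocated 1:1:1:1, so 120/4 = 30 per arm. Assumed, because the documents give none: a shift of 2, 5 or 10 points on each self-reported component, a baseline-to-follow-up correlation r of 0.3 to 0.7, and an SD of 10 to 15 points, equal at both times.

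1. Shift d in the LE8 composite = (4/8) × component shift = 1.0, 2.5 or 5.0 points.
2. Let true follow-up be Y = rB + τG + error, with G the arm indicator, τ the true effect and B the true baseline. If the recorded baseline is B* = B + dG, then Y = rB* + (τ − rd)G + error. The adjusted estimate is biased by −rd. A simple change score is biased by −d.

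| LE8 shift d | r = 0.3 | r = 0.5 | r = 0.7 | Change score |
|---|---|---|---|---|
| 1.0 | −0.30 | −0.50 | −0.70 | −1.0 |
| 2.5 | −0.75 | −1.25 | −1.75 | −2.5 |
| 5.0 | −1.50 | −2.50 | −3.50 | −5.0 |

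3. Simulation check (20,000 two-arm comparisons, 30 per arm, SD 12, r = 0.5, d = 2.5): mean bias −1.28, against −1.25 from the formula.
4. Sampling error of the adjusted arm difference: SE = SD × sqrt((2/30)(1 − r²)), half-width = 1.96 × SE.

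| Half-width of 95% CI | r = 0.3 | r = 0.5 | r = 0.7 |
|---|---|---|---|
| SD 10 | 4.83 | 4.38 | 3.61 |
| SD 15 | 7.24 | 6.57 | 5.42 |

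At matching r, the adjusted bias is below the half-width throughout this grid. It comes close only in the extreme corner (3.50 against 3.61).

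5. If the same shift d also persists at follow-up, the adjusted bias becomes d − rd = (1 − r)d, which is positive, and the change-score bias becomes 0. For d = 2.5 and r = 0.5 that is +1.25 in place of −1.25. Size and sign therefore depend on whether the shift lasts, which the documents cannot settle.

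**The case against.** The strongest reply is that the order is only inferred. The word that introduces randomisation links it to consent. The paragraph on the assessment opens without a time marker and may simply list the T0 content by topic. The article sends the reader to Figure 1 for the timeline, and that figure could not be seen here. This stands: a reader might infer that the baseline values are known to be post-randomisation, and the documents do not support so firm a statement. But the text does set out a sequence, that sequence puts open allocation first, and nothing visible corrects it.

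Three further inferences also fail:
- **That participants answer with the device already in hand.** On the same reading of the text order, devices and saliva come after the questionnaires. At most the arm is known.
- **That risk perception enters the models as a covariate.** Only lifestyle scores, lipids and SCORE2 are named as modelled outcomes.
- **That the bias is large or has a known direction.** A composite shift of 5 points needs 10 points on every self-reported component merely from learning the arm. The direction reverses if the shift persists.

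It can also be said that the affected analyses are exploratory and unpowered, and that reporting bias is already acknowledged. The first limits the weight of the point. The second does not answer it, because the acknowledgement concerns outcomes, and standardised questionnaires across arms do not change when the baseline is taken.

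**Conclusion.** The point holds as a weakness in how the T0 order is fixed. Followed as written, the text allows the self-reported half of the LE8 baseline to be given with the arm known, and that baseline is then used for adjustment. Under the assumed ranges, and if the shift is confined to baseline, the adjusted estimate is biased by about 0.3 to 3.5 points, usually well inside the confidence interval at 30 per arm. If the shift persists at follow-up, both size and sign differ.

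The consequence is limited to the exploratory lifestyle-score comparisons and the T0 risk-perception measurement. A reader might infer that the trial's main conclusions are at risk. They are not: the three progression criteria (recruitment, completeness of outcome data, GPs' willingness) do not use the baseline lifestyle score. If Figure 1 or site practice already has the questionnaires first, a clarifying sentence settles the matter.

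**What to change.** State the T0 order explicitly: consent; eligibility check; all T0 questionnaires and measurements completed and recorded in REDCap; randomisation and disclosure of the arm; then arm-specific saliva collection or device hand-out. REDCap is already named both for randomisation and for recording participants' data, so the two steps can be tied together in one place.

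For participants already enrolled, record whether their T0 forms preceded randomisation, so that the lifestyle analyses can be read accordingly.

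The cost is a small change of workflow within the same visit. Sample size, visits and outcomes stay as they are. With the questionnaires first, allocation cannot shift the baseline (d = 0 at T0). The change does not remove reporting bias at follow-up: a shift of d there would still appear in the estimate as +d. That remains the limitation which the article already acknowledges.

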#### T1 (1 month post-enrolment)

All participants will be informed about their lifestyle profile through direct communication, including telephone contact, and will receive written materials via email outlining standard behavioral interventions to reduce cardiovascular risk, regardless of group assignment. Participants in groups 3 and 4 will receive detailed explanations of their genetic risk results derived from the PRS analysis. This will include information about their categorized risk level and the implications for their cardiovascular health, helping them understand how their genetic predisposition may affect their overall risk.

#### T2 (6 months post-enrolment)

All participants will be contacted by GPs by telephone for a follow-up assessment where they will complete the questionnaire to monitor changes in their health behaviors. Participants will be extemporarily informed of their progress and any updated lifestyle classification. Moreover, extra counseling and support will be provided to reinforce positive lifestyle changes.

